#### Costs

Health plan costs are one of our secondary outcomes, as we are interested in how total health plan costs differed between A/C users and nonusers. Costs will be estimated by applying internal unit costs developed and tested in previous studies [111,112] to the HMO patient-level utilization measures, with the final cost variables acting as proxies for HMO resource cost. We are interested in the effect of patient-level factors--in particular, patients' use (or not) of A/C services on health care costs. Admittedly, the challenges of analyzing typical cost data are well known and significant; these include 1) having a large proportion of non-users (i.e., zero costs); 2) the fact that non-zero costs are usually right-skewed; and 3) heteroscedasticity. Assuming these challenges exist in our study cost data, we will tackle them by exploring transformation models and generalized linear models (GLM). Transformation models convert skewed cost data using a transformation (e.g., log-normal) to a better-behaved distribution (i.e., one more normal and symmetric, homoscedastic, less skewed, promoting more efficient estimation). A complication of transformations is possible re-transformation bias in switching from the transformed scale to the original dollar-based scale. GLM avoids re-transformation bias but can be highly imprecise if the residual pattern is misspecified. We will explore both model forms to determine the most accurate and descriptive approach for our study data. Cost analyses will be performed in STATA version 11.

### Phase 3 Sample Size

We based our Phase 3 sample size determination on the BPI short form severity (BPI-S) and interference (BPI-I) subscales. Although these outcome measures are highly recommended for pain studies [82], it is difficult to find the appropriate statistics reported in the literature, that are required for design purposes. We have relied on the findings from the SCAMP intervention [113,114] and Tan's and colleagues' validation study of the use of the BPI for chronic nonmalignant pain [115], who reported SD = 2 (approximately) for both the severity and interference subscales of the BPI in large samples of patients with nonmalignant pain. Changes on the order of 1-3 points have been cited as being relatively common [116] and within the range of change found in the SCAMP intervention [113,114]. Collectively, these sources suggest that an attainable and clinically meaningful effect size would be 0.50, which translates into a difference between mean changes of 1 unit (absolute). For 100 patients in each of two groups, assuming a 0.5 correlation between pre- and post-measurements, using a conventional two-sample t-test with a two-sided significance level of 0.025 (to allow for two tests), the power would be slightly over 90% to detect a 1 unit treatment effect. The analysis we intend to use would be more efficient, because it would adjust for baseline BPI values, but we might also want to include explanatory factors into the analysis, which might decrease efficiency. Consequently, we propose group sizes of 200, for a total of 1, 200 - that is a total of 200 participants each for those receiving acupuncture and chiropractic services as well as two matched comparison CMP participants for each of these index participants for a total sample size of 1, 200. Table 6 shows sample and effect sizes for a number of recent studies of related pain conditions utilizing related measures as well as anticipated effect size estimates for the current study. While these comparative clinical trials may have possibly produced greater effect sizes than we will observe in this observational study, our proposed group size is substantially larger than those reported for each of these studies.

**Table 6 T6:** Sample and Effect Sizes for Related and Current Study

Study	Condition	Treatment	Assessment Scale	Group size	Effect size
Cherkin, 2009 [19]	chronic LBP	acu	RMDQ	160	0.46
Cherkin, 2009 [19]	chronic LBP	acu	bothersomeness	160	0.42
Liang, 2011 [118]	chronic neck pain	acu	NPQ	81	0.24
Franca, 2008 [119]	tension headache	acu v PT	VAS pain	16	2.0
Molsberger, 2010 [120]	shoulder pain	acu v UC	VAS pain	150	1.01
Hondras, 2009 [121]	LBP > 55 yrs	chiro v UC	RMDQ	90	0.3
Kroenke, 2009 (as reported in Krebs, 2010)[113,114]	musculoskeletal pain	Rx/self care v UC	BPI-S, BPI-I	125	0.56 (BPI-S) 0.59 (BPI-I)
Current study	musculoskeletal pain	acu v UC	BPI-S & BPI-I	200	0.5*
Current study	musculoskeletal pain	chiro v UC	BPI-S & BPI-I	200	0.5*

Note: LBP - lower back pain; acu - acupuncture; chiro - chiropractic care; LM - light massage; RMDQ - Roland Morris Disability Questionnaire; NPQ - Northwick Park Neck Pain Questionnaire; BPI-S - Brief Pain Inventory Severity Subscale; BPI-I - Brief Pain Inventory Interference Subscale; * estimated ES

To estimate available numbers of CMP patients who may receive A/C care for the Phase 3 prospective cohort study, we examined the number of health plan referrals for A/C care during a recent three-year period. Referral patterns for A/C among health plan members with CMP (see Figure 3) are fairly stable, with an average of 330 acupuncture and 303 chiropractic referrals monthly; therefore, we should have an adequate recruitment pool (estimate of 15, 192 A/C referrals with CMP over the two-year recruitment period) to meet the target enrollment for this phase of the study.

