### Phase 3 participants and recruitment

***Index ***participants (i.e., those with an incident A/C referral, n = 200 acupuncture and 200 chiropractic) and matched ***comparison ***participants in this prospective portion of the study must meet the overall CMP eligibility criteria listed in Table 1 and be able to read and respond to assessment questionnaires. Both index and comparison patients must have had no A/C treatment over the previous six months to ensure that we are prospectively following a new episode of A/C care. We purposefully minimized exclusion criteria to ensure that study findings are as broadly representative of the CMP population as possible.

Health plan members will be recruited over a two-year period through a weekly EMR review to identify CMP patients referred for A/C. Those referred for A/C will be mailed an invitation to the study, including a brochure and letter describing the study, and indicating that a staff member will call soon to tell them more about the study. There will also be a study website where prospective participants can log on to learn more about the study and eligibility or opt out if they so choose. Eligible participants will be guided through the consent process and baseline assessments by an interviewer or online, according to their preferences.

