**Chronic Musculoskeletal Pain Patient Measures:**					
**Pain and related disability (patient-reported, primary outcomes)**					
Pain Severity (BPI-SF subscale)	√	√	√	√	√
Pain Interference (BPI-SF subscale)	√	√	√	√	√
Pain Bothersomeness (single item)	√	√	√	√	√

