#### Primary outcomes: Pain and related disability

Two subscales--the 4-item pain severity and the 7-item pain interference subscales--from the short form of the Brief Pain Inventory (BPI-SF)[84,85] will be used to assess pain and related disability. The BPI has sound psychometrics and has been widely adopted for clinical pain assessment, epidemiological studies, and studies of treatment efficacy. We will also include a measure of how bothered participants are by their pain. This instrument uses a 0 to 10 scale of "symptom bothersomeness, " where 0 represents "not at all bothersome" and 10 is "extremely bothersome." This question has been frequently used in studies of back pain [18,19,86] and shown to have adequate construct validity [87].

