### Phase 3 Data Analysis

#### Patient-reported outcomes

For the patient-reported outcomes in Phase 3, we will examine differences in baseline measures between participants with and without data at the 1-, 3-, 6-, and 12-month  follow-ups. Variables related to missingness will be included in the main analyses as covariates to reduce bias in the estimates [109,110].

We will use multilevel modeling to examine differences across time in primary (pain intensity/interference/bothersomeness) and secondary patient-reported outcomes between A/C users and matched comparison participants. Two parameters (linear and quadratic slope) will characterize change across time, with linear slope capturing initial rate of change and quadratic slope reflecting the degree to which the change slowed (or increased) over time. Thus, the quadratic model for time (baseline and 1-, 3-, 6-, and 12-month follow-ups) captures nonlinear change across time. Unlike repeated measures analysis of variance, multilevel modeling does not require data at all time points from each subject, so data from all subjects will be included in analyses. Depending upon the distribution, normal, logistic, or Poisson models will be used. Importantly, these analyses can be adjusted using additional information collected from participants during the baseline assessment that we may identify in Phase 2 as influencing A/C decision-making. This will better control for factors not available during comparison patient identification when only EMR data will be available for matching/clustering.

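### The Phase 3 significance level of 0.025 allows for two tests, but the protocol lists three primary outcomes and plans two separate therapy contrasts

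*Protocol article*

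**What the plan says.** The Phase 3 Sample Size section begins "We based our Phase 3 sample size determination on the BPI short form severity (BPI-S) and interference (BPI-I) subscales". It then takes 100 patients per group and a 1-unit difference, and computes power "using a conventional two-sample t-test with a two-sided significance level of 0.025 (to allow for two tests". The result given is slightly over 90%. The planned groups are larger: 200 index patients per therapy, each with two matched comparison patients, 1,200 in total.

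The list of primary outcomes is longer than the two measures used for sizing.

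- Table 5 has the heading "Pain and related disability (patient-reported, primary outcomes", with three rows beneath it. The third is "Pain Bothersomeness (single item".
- The text section on primary outcomes describes the two BPI subscales and continues "We will also include a measure of how bothered participants are by their pain".
- The Phase 3 analysis section will model "differences across time in primary (pain intensity/interference/bothersomeness) and secondary patient-reported outcomes between A/C users and matched comparison participants".

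On the number of comparisons, the recruitment section sets index groups of "n = 200 acupuncture and 200 chiropractic". Table 6 gives the current study two rows, one for acupuncture against usual care and one for chiropractic against usual care, each with group size 200 and effect size 0.5.

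**The concern.** A per-test level justified by a count of tests is a statement about the planned confirmatory family. Here the count is two, while the outcome list gives three and the design gives two contrasts. The article states no testing order, gatekeeping or composite that would bring the number down to two.

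At stake is what a positive result would mean. If success on any primary outcome is read at 0.025, the chance of at least one false positive is above the 5% that the split implies, by an amount that depends on which family was intended. The conflict is between passages of the article itself, so a separate analysis plan could resolve it but would not make these passages agree.

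**Working it through.** **Inputs.** From Phase 3 Sample Size: SD about 2, pre-post correlation 0.5, difference 1 unit, 100 per group, two-sided 0.025, planned 200 index patients with two comparison patients each. From Table 5 and the Phase 3 analysis section: three primary outcomes. From the recruitment section and Table 6: two therapy contrasts. Assumed, because the documents do not give it: a common correlation rho between outcomes within a therapy, varied from 0.5 to 0.9. The two therapies are treated as independent because each has its own comparison patients: 2 × (200 + 400) = 1,200.

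**1. The plan's own power figure.**

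- SD of change = 2 × √(2 × (1 − 0.5)) = 2.
- Standard error = 2 × √(2/100) = 0.283, and 1/0.283 = 3.54.
- Power at 0.025 = Φ(3.54 − 2.24) = 90.2%. The noncentral t gives 89.8%.

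The stated figure reproduces. Two tests at 0.025 give a bound of 2 × 0.025 = 0.05, which is the implied family level.

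**2. How many tests there are.**

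- Three outcomes for one therapy, or three outcomes for one pooled A/C contrast: 3 tests.
- Two BPI subscales for each of two therapies: 4 tests.
- Three outcomes for each of two therapies: 6 tests.

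**3. Family-wise error at 0.025 per test.** For k independent tests it is 1 − 0.975^k. The correlated values come from a simulation of 1,000,000 draws of correlated normal test statistics.

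| Tests | Bonferroni bound | Independent | rho 0.5 | rho 0.7 | rho 0.8 | rho 0.9 |
|---|---|---|---|---|---|---|
| 2 (as stated) | 5.0% | 4.9% | – | – | – | – |
| 3 | 7.5% | 7.3% | 6.5% | 5.7% | 5.2% | 4.4% |
| 4 | 10.0% | 9.6% | 9.0% | 8.4% | 8.0% | 7.1% |
| 6 | 15.0% | 14.1% | 12.6% | 11.1% | 10.1% | 8.5% |

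**4. Power once the level matches the family** (t-test, 1 unit, SD of change 2):

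| Per-test level | 100 v 100 | 200 v 200 | 200 v 400 |
|---|---|---|---|
| 0.025 | 89.8% | 99.7% | 99.98% |
| 0.05/3 = 0.0167 | 86.8% | 99.5% | 99.96% |
| 0.05/6 = 0.0083 | 80.7% | 99.0% | 99.91% |

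The size needed for 90% power rises from 100 per group to 109 (three tests) or 123 (six), both below the planned 200. The margin is smaller for smaller effects. At effect size 0.3, the value in Table 6 for the cited chiropractic trial, 200 v 400 gives 88.8% at 0.025 and 79.3% at 0.0083.

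**The case against.** The best defence is that the two tests are the two BPI subscales within each therapy. Each current-study row of Table 6 pairs exactly those two subscales with one therapy, and each therapy has its own comparison patients. Acupuncture and chiropractic are then separate questions, and whether to control error across separate questions is a legitimate choice. This has real force against a count of six. It does not rescue the count of two, because bothersomeness is named as primary in three places. The pooled reading, which the analysis section's reference to A/C users permits, also leaves three tests.

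It can also be said that 0.025 is only a sizing assumption for a t-test that the authors do not intend as the main analysis, that the 5% family level is never written down, and that a non-randomised cohort is not a confirmatory trial. All three are true and limit the weight of the point. Even so, the section chose to allow for multiplicity and gave a number, and that number disagrees with the outcome list. The remarks that decline pre-specification and statistical decision-making belong to Phase 1 and do not explain a Phase 3 allowance.

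Two stronger readings are tempting but unsupported. A reader might infer that the false-positive risk is simply two to three times what was intended. That needs one family across both therapies, which the protocol suggests but never states. A reader might also count the linear and quadratic slopes as separate tests and arrive at twelve. The analysis section says that the two parameters together describe change over time. It does not make each a primary test, and treating the two estimates as independent would not be justified.

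**Conclusion.** The point holds as an inconsistency between the stated allowance and the listed primary tests. Against an implied 5%, family-wise error is 7.3% for three independent tests, or about 5.2% to 6.5% at assumed correlations of 0.8 to 0.5. For six it is 14.1%, or about 10.1% to 12.6%. The size therefore depends on a choice of family that the protocol leaves open. In the mildest case, three tests with outcomes correlated at about 0.9, the error actually falls below 5%, although the count of two is still wrong. The six-test figures assume separate therapy contrasts with independent comparison groups. The consequence is for error control and not for sample size: a reader should not infer that Phase 3 is too small for the 1-unit difference it targets.

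**What to change.** State whether the 5% applies to each therapy or across both. Apply Holm, or a Bonferroni split, over all the primary tests in that family: three tests (0.05/3 = 0.0167) or six (0.05/6 = 0.0083), with one defined contrast per test. Alternatively, if the sponsor intends only the two BPI subscales to be confirmatory, relabel bothersomeness as secondary in Table 5, the outcomes section and the analysis section. The level 0.025 is then right per therapy, and 0.05/4 = 0.0125 across both.

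Restate the power sentence at the chosen level. For 100 per group, t-test power falls from about 90% to about 87% (three tests) or 81% (six). For the planned 200 versus 400 it stays at about 99.9% before attrition.

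No extra patients are needed for the 1-unit target. Relabelling bothersomeness would be more than an edit, because it changes the primary outcome list, so that decision belongs to the sponsor and should be made before outcome data are seen.

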**Figure 3 F3:**
[figure not shown]
**Health Plan Patients with Chronic Musculoskeletal Pain (CMP) Receiving New* Acupuncture and or Chiropractic Care (A/C) Referral**.

### Ethical Approval

Written consent will be obtained from each participant in Phases 2 and 3 and from those completing the out-of-plan A/C survey in Phase 1. For the data-only portion of Phase 1, health plan members' contracts with the HMO provide consent for use of their data in HMO-sponsored research studies. This study protocol was approved by the institutional review boards (IRB) of Kaiser Permanente Northwest, University of Arizona, and Oregon Health and Science University. This study protocol is registered with http://www.clinicaltrials.gov (NCT01345409).

## Discussion

We expect that successful completion of this study will provide an evaluation of the outcomes--from the perspectives of patients, providers, and health services utilization--associated with the real-world use of A/C services. By comparing the results of the EMR-only analyses with the more comprehensive results available in Phase 3, we will be able to identify the strengths and weaknesses of EMR-alone analyses and potentially identify the most critical additional data needed. We further anticipate that the trio of EMR-based analyses, qualitative assessment, and prospective cohort studies will provide a clearer understanding of the decision-making processes behind the use of A/C for CMP; these will also provide a transportable methodology that can be applied to other health care settings, CAM treatments, and clinical populations.

With regard to advancing our understanding of patients' use of CAM in everyday practice settings, much CAM research to date has focused narrowly on "early adopters" (those likely to use CAM services regardless of barriers [117]). Yet within our cohort, cost and access barriers are substantially reduced, allowing us to study other factors (see Figure 1) influencing A/C care receipt and outcomes and to develop a comprehensive characterization of A/C use patterns and outcomes in patients with increasing access to such CAM services. An important goal of this study is to clarify how CMP patients use A/C compared to conventional care (to augment or replace it), when and why patients disclose A/C use to allopathic providers, and how such practices may vary by patient characteristics. Our mixed methods approach will help us develop a better understanding of the process behind the decision to initiate (patients), recommend (allopathic providers), and continue (patients and providers) A/C care for the treatment of CMP. Finally, studying this in everyday treatment settings allows us to consider the range of services received in A/C care (e.g., needling or spinal manipulation vs. whole systems-based care) and variation by characteristics of the CMP patient and/or A/C provider.

In addition to advancing our understanding of real world A/C practices and their impact on CMP, this study affords us the opportunity to build upon the increasingly available EMR systems to conduct research that may be more broadly adopted to better understand the real world interplay of conventional medicine and A/C services. Using EMRs exclusively may limit information on important variables (covariates) on which to match or cluster like patients. However, by augmenting data sets through direct reports by providers and patients regarding important decision-making factors suggested by qualitative findings, we may substantially reduce potential confounding in comparing those who do and do not receive A/C treatment. Thus, we can identify whether widely available data in EMR and administrative systems can be used to adequately forecast patients' outcomes and evaluate the extent to which supplementation from additional patient- and provider-collected information is a necessary adjunct to EMR-based data analysis.

Finally, our MCG-focused methodology gives us a unique opportunity to conduct patient-centered research; that is, to identify like groups based upon actual individual patient care characteristics rather than hypothetical group averages. A typical RCT may not include enough participants to form homogeneous clusters for separate evaluation, yet an EMR database of a large clinical population like the CMP sample described here does include sufficient numbers of patients with similar characteristics and disease severity to form clinically meaningful clusters as the basis of the analyses. Accordingly, this research may allow us to address the clinical question as follows: for whom does supplementary CAM care result in clinically significant improvements in pain severity and overall functioning? Our planned MCG methodology will allow us to identify the characteristics of CMP patients for whom A/C may have the greatest impact on satisfaction, functioning, clinical, and QOL outcomes; it will also clarify whether the timing of services relative to conventional care and the course of the CMP affects such outcomes.

## List of abbreviations

CAM: complementary and alternative medicine; A/C: acupuncture/chiropractic care; ACU: acupuncture; CHIRO: chiropractic; LM: light massage; CP: chronic pain; CMP: chronic musculoskeletal pain; TMD: temporomandibular disorders; HMO: health maintenance organization; KPNW: Kaiser Permanente Northwest; EMR: electronic medical record; AR: administrative record; ICD-9: International Statistical Classification of Diseases - 9^th ^edition codes; CPT: current procedural terminology codes; MCG: matched comparison groups; SD: standard deviation; ES: effect size; GLM: general linear models; RCT: randomized clinical trial; QA: quality assurance; MD: medical doctor; DO: doctor of osteopathic medicine; NP: nurse practitioner; IMMPACT: Initiative on Methods, Measurement, and Pain Assessment in Clinical Trials; BPI-SF: Brief Pain Inventory-Short Form; BPI-S: Brief Pain Inventory Severity Subscale; BPI-I: Brief Pain Inventory Interference Subscale; PGIC: Patient Global Impression of Change; NHIS: National Health Information Survey; PHQ-8: Personal Health Questionnaire-8 item version; GAD-2: Generalized Anxiety Disorder-2 item version; RMDQ: Roland Morris Disability Questionnaire; NPQ: Northwick Park Neck Pain Questionnaire
